### 2.6. Recruitment

All the patients who have suffered a first ischemic stroke with a neurologic deficit and have been admitted in the Acute Stroke Unit of the Neurology Department of our Cruces University Hospital will be assessed by a Rehabilitation Medical Doctor (RMD) with expertise in neuro-rehabilitation. The assessment will be done in the first 48–72 h from the stroke. The survivors who need conventional rehabilitation treatment will start it within the first 72 h from the cerebrovascular attack unless they present a medical contraindication, such as hemodynamic instability or others.

The rehabilitation treatment will be at a maximum tolerated intensity, daily from Monday to Friday till the end of the hospitalization. Before the discharge of the patient, an RMD will reassess the discharge destination to home, rehabilitation hospital as inpatient, or nurse home care.

At 6 months after the stroke, all the survivors who fulfill the inclusion criteria and who are willing to take part in the research will be recruited, including their caregivers. Those who will not be included are patients without familial support, or a caregiver and the formal caregivers of stroke patients will not be included if the patient does not want to take part in the study. The sample will be divided into intervention and control groups in consecutive order (Figure 1).

Participants will be enrolled in the external consultation at neuro-rehabilitation at Cruces University Hospital in Spain. We will include eligible individuals admitted in consecutive order, to avoid bias, taking into account the inclusion and exclusion criteria. All the participants will be volunteers, having signed the informed consent. The researchers responsible for the recruitment of patients will assure that the informed consent is collected with all the rigor it requires.

The assignment to the control/intervention group will be made through a probabilistic computer algorithm with a ratio of 1: 1 between groups. The Bioinformatics and Statistics Platform of Biocruces Bizkaia Institute will be responsible for the creation of the algorithm using a simple allocation mechanism in permuted blocks of variable size. Opaque envelopes will be used to guarantee the concealment of the generated sequence. The randomization list will remain on the platform at all times, guaranteeing the concealment of the sequence of randomization.

Afterward, the devices will be installed at participants’ homes.

### 2.7. Protocol

The treatment assessment schedule is displayed in Table 1 and Table 2. All patients will be treated through regular practice, and the patients of the intervention group will be supported by the STARR platform.

### 2.8. Control Group

The controls will continue following the conventional home recommendations and the standard of care. They will be scheduled to carry out health care recommendations and medical and rehabilitation guidelines at home. The exercises will also be scheduled: aerobic exercises, resistance-potentiation, and stretching. Visits will be made every six months during the first year of follow-up and then annually.

### 2.9. Intervention Group

Cases will integrate into their daily routines the designed system (STARR App, DSS, and wearables), measuring at least once a day the vital signs and motor activity during outdoor activities and cycloergometer/pedal exercising. As medical doctors, we will promote a healthy diet, no alcohol or smoking consumption, weight control, blood pressure control, glycemic control, and complications control (e.g., pain, spasticity, falls, infections, etc.).

The designed application will have alarm systems, both for the patient and for the caregiver. The alarms can guide the patient through actions that can recommend to call or go to your primary care physician or go to the emergency services.

The commercial wearable devices will be chosen according to different characteristics: Price, Bluetooth connection, valid for iOS/Android, battery duration, and user’s opinions.

The commercial wearables should be easy to use, comfortable, cheap, and accurate in order to be accessible for the users.

The survivors and the caregivers will be trained about the use of the devices and also about the measures they have to take (e.g., weight, blood pressure, waist circumference) during a period of one week to 10 days.

In case of any technical problem, the user will have a telephone number to put in contact with technical support. If it’s not possible to solve the problem remotely, a technician will go to the participant’s home.

### 2.10. Outcome Measures

The primary clinical focus in this pilot trial is the evaluation of self-management of the stroke survivors. The proposed primary outcome will be measured by the validated Southampton Stroke Self-Management Questionnaire (SSSMQ) and Family needs of stroke patient questionnaire.

A series of secondary outcomes will be evaluated at different time points, such as the effectiveness of stroke self-management interventions. They rely upon the following items:-Physical function (PF) assessed by the modified BI and Lawton index.-Risk factor reduction (blood pressure, analytical profile -glycemia, HbA1c, lipids, weight, heart rate control, medication compliance).-Self-management behaviors by self-reported information on lifestyles: diet assessed by the Mediterranean diet assessment tool, exercise assessed by tracking with the wearables, smoking, and alcohol consumption.-Healthcare resource utilization by the information available in the public health system in Osakidetza, Cruces university hospital.-Knowledge of condition to assess whether there is a relationship between health literacy and control of cardiovascular risk factors, number of complications, number of recurrences, low adherence to pharmacological and non-pharmacological treatment, and self-management behaviors.-Mood and social isolation by Goldberg scale that measures anxiety and depression.-Stroke Self-management questionnaire (SSMQ).

Other secondary outcomes will be focused on the International Consortium for Health Outcomes Measurement (ICHOM), such as survival, disease control, and acute complications.

All the questionnaires and measurements for the achievement of the outcomes will be collected through face-to-face medical visits in the neuro-rehabilitation department.

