### 2.4. Study Design

We will perform a prospective, randomized, parallel group, open, and unicentric pilot trial. We will analyze the data from 40 patients between 18 and 80 years old who have had an ischemic stroke, and whose family or friend caregivers are followed at Rehabilitation Unit at Cruces University Hospital. Two groups will be formed. The control group will get conventional treatment from the acute to the chronic phase of stroke, and the intervention group will get a conventional treatment to the end of the subacute phase. However, in the chronic period, they will use the developed STARR System, as well as commercial wearables.

The main stages of stroke recovery are defined by temporal terms (acute, subacute, and chronic). The acute stage refers to the first 7-days-period of the stroke event. The subacute stage represents the patients from the first week till 6 months, dividing this period in two: early subacute (up to 3 months) and late subacute (from 3 to 6 months). The chronic stage is beyond 6 months when brain repair processes suggest that the majority of the recovery has occurred [22].

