## Figures and Tables

**Figure 1 mps-02-00050-f001:**
[figure not shown]
Diagram of the study.

**Table 1 mps-02-00050-t001:** Schedule of the trial variables for patients.

Stroke Survivors	Variables/Scales	Event Visit (a) Month 0	Baseline Visit (b) Month 6	First Visit (c) Month 9	Final Visit (d) Month 12
Inclusion	Age	x	x		
	Stroke characteristics and type	x	x		
	Modified Barthel Index	x	x		x
	Modified Rankin Scale	x	x		x
	Mississippi Aphasia Screening Test [MAST]	x	x		x
	Montreal Cognitive Assessment [MoCA]	x	x		x
	Gijon’s social-familial evaluation scale	x	x		
	Comorbidities	x	x		
	Charlson Comorbidity Index	x	x		
Socio Demographic	Gender, ethnic group, deprivation index, hand dominance, education level, type of job, hobbies	x	x		
Clinical/ Neurological	Cardiovascular risk factors	x	x	x	x
	Neurological physical examination: Medical Research Council Scale [MRC]	x	x	x	x
	Mississippi Aphasia Screening Test [MAST]	x	x		x
	Montreal Cognitive Assessment [MoCA]	x	x		x
	Functional Ambulation Categories [FAC]	x	x	x	x
	10 m walking test/6 min walking test	x	x	x	x
	Berg Balance Scale [BBS]	x	x	x	x
	Frenchay Arm Test [FAT]	x	x	x	x
	Asworth Modified Scale for Spasticity	x	x	x	x
	Fatigue Severity Scale [FSS],	x	x	x	x
	Line Bisection Test	x	x	x	x
	Disphagia Sensitivity Campimetry	x	x	x	x
	Pain Analogic visual scale for pain Analgesic treatment consumption	x	x	x	x
	Depression and Anxiety: Golberg Scale	x	x	x	x
	Stress	x	x	x	x
	Weight, Height, BMI, waist size, waist-to-hip ratio	x	x	x	x
	Blood pressure, heart rate, glycemia	x	x	x	x
	Need of upper limb orthoses, lower limb orthoses, and canes and wheelchair use in outdoor activities	x	x	x	x
Health Literacy	Test of Functional Health Literacy in Adults Stroke Patient Education Retention	x	x		x
Usability	System Usability Scale			x	x
Life Style	Mediterranean Diet Assessment Tool Physical activity/Exercise Toxic consumption	x	x	x	x
Blood Test	Lipidic profile (total cholesterol, high-density lipoprotein (HDL), low-density lipoprotein (LDL), cholesterol), glycemia, proteins, albumin, HbA1c, Apoprotein B, and Apoprotein A1	x	x		x
Activities of Daily Living	Modified Barthel Index (BI) Lawton Index	x x	x x		x x
Quality of life	SF-36 Stroke Impact Scale (SIS)	x x	x x		x x
Self-Management	The Southampton Stroke Self-Management Questionnaire (SSSMQ)		x	x	x
	Satisfaction Questionnaire		x		x
	Quebec User Evaluation of Satisfaction with Assistive Technology			x	x
Adherence	Post-stroke checklist		x		x
	Non-pharmacological				

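### Exercise is defined by wearable tracking, a part of the STARR intervention, which conflicts with the exercise item that Table 1 schedules for all patients

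*Protocol article*

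**What the plan says.** **The outcome.** Section 2.10 introduces this secondary outcome as "Self-management behaviors by self-reported information on lifestyles" and lists four behaviours: diet, exercise, smoking and alcohol. Diet has a named questionnaire. For exercise the text reads "exercise assessed by tracking with the wearables, smoking, and alcohol consumption". The section closes by saying that all questionnaires and measurements for the outcomes are obtained at face-to-face visits.

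**Who has the wearables.** Section 2.4 says of the intervention group that "in the chronic period, they will use the developed STARR System, as well as commercial wearables", and lists wearables among the STARR components. Section 2.9 says "Cases will integrate into their daily routines the designed system (STARR App, DSS, and wearables". Section 2.7 adds that "the patients of the intervention group will be supported by the STARR platform". For the other arm, Section 2.8 says "The controls will continue following the conventional home recommendations and the standard of care"; it schedules exercises but mentions no device or tracking.

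**The schedule.** Table 1 has a lifestyle row, "Mediterranean Diet Assessment Tool Physical activity/Exercise Toxic consumption", marked at the event, baseline, first and final visits. It is not limited to an arm and names no exercise instrument. Section 2.12 says that all participants have the same reassessments. Section 2.6 places device installation after allocation, in participants' homes, without saying which arm.

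**The concern.** A between-group comparison needs the same measurement in both arms. Here the only instrument named for exercise is part of the experimental treatment. If Section 2.10 is followed literally, exercise is tracked in the STARR arm and not in controls. If Table 1 fills the gap for controls, the two arms are measured by different methods, and a difference between them could come from the method alone.

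Tracked activity in the STARR arm also depends on the device being used. Section 2.9 has these patients record motor activity during outdoor activity and pedal exercise, and the mini-bike is itself a STARR component in Section 2.4. The recorded quantity therefore mixes exercise with use of the system.

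The Discussion expects the intervention to promote physical activity. At stake is whether the trial can show that against controls.

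**Working it through.** No figure in the plan depends on this point, so the check sets the passages side by side.

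**Inputs**
- Instrument for exercise: wearable tracking only (Section 2.10).
- Wearables: described for the intervention group (Sections 2.4, 2.7, 2.9); none mentioned for controls (Section 2.8).
- Installation: after allocation (Section 2.6).
- Trial visits: baseline at month 6, first at month 9, final at month 12 after the stroke (Table 1).

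**Where a value can exist**

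| Visit | Tracking, STARR arm | Tracking, control arm | Table 1 item, either arm |
|---|---|---|---|
| Baseline, month 6 | no, devices not yet installed | no | marked |
| First, month 9 | yes | none described | marked |
| Final, month 12 | yes | none described | marked |

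Cells needed for a comparison adjusted for baseline: 2 arms × 3 visits = 6.

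Cells that tracking can fill: 1 arm × 2 visits = 2 of 6.

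**If controls also had devices.** Section 2.6 names no arm, so suppose that both arms receive them. Tracking then fills 2 arms × 2 visits = 4 of 6 cells. Baseline is still empty in both arms, and controls would be using part of the intervention, contrary to Sections 2.4 and 2.8.

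**Conflicts found**
1. Within Section 2.10, device tracking sits under a heading of self-reported information. Home tracking also does not fit the closing sentence on face-to-face collection.
2. Between Section 2.10 and Table 1, the item is marked at the event and baseline visits, before installation. Wearables cannot supply those values, so the Table 1 item must come from some other method, at least at those visits.
3. Between Section 2.10 and Section 2.12, the same reassessment for everyone is not possible with an instrument that only one arm is described as using.

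**The case against.** The strongest reply is that control-arm exercise data are planned. The Table 1 row carries no arm restriction, Section 2.12 promises the same reassessment to all, and Section 2.10 itself calls the information self-reported. On this view the mention of wearables is loose wording, a comparison can be made from the Table 1 item, and its instrument is a detail that an article may leave to the full protocol.

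Much of this stands. A reader might infer from Section 2.10 that exercise is entirely missing in controls and that only an uncontrolled trend within the STARR arm would remain. The documents do not support that. The event and baseline marks precede any device use, so at those visits future controls and future STARR patients are assessed alike, and the follow-up marks are not limited to one arm either.

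The reply does not remove the defect. The article does not merely omit the instrument. It states one, and that one cannot produce the values that Table 1 schedules. Nor does the unspecific wording in Section 2.6 give controls a wearable; read with Sections 2.4, 2.7 and 2.9, it most naturally refers to the STARR arm. Section 2.8 is silent rather than explicit, so the absence of devices in controls is a well-supported inference and not a stated fact.

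**Conclusion.** The point holds as a conflict over how exercise is measured. Under the Section 2.10 definition the outcome has no baseline value in either arm and no comparable control value: two of six cells can be filled. Combining tracked STARR data with the Table 1 item in controls would confound arm fully with method. The documents do not allow the size or direction of the resulting bias to be estimated.

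The conclusion assumes that controls receive no wearables. The lack of a baseline value rests only on the order of events in Section 2.6 and does not need that assumption.

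The reach is limited to one of four behaviours in one secondary outcome. The primary outcome uses questionnaires and is unaffected.

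A reader might extend the point to blood pressure, weight, heart rate and glycemia, since STARR devices record several of these at home. The text does not support that: Section 2.10 says that outcome measurements are made at face-to-face visits, Table 1 lists these variables at every visit, and nothing names home readings as their source.

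**What to change.** 1. In Section 2.10, define the exercise outcome as the physical activity item in Table 1, collected with one named instrument and in the same way in both arms at baseline, month 9 and month 12.
2. Describe wearable activity data as adherence or exposure data within the STARR arm, with no between-group test.
3. In Section 2.6, state which arm receives the devices, so that it agrees with Sections 2.4, 2.8 and 2.9.

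The cost is small. The item is already on the schedule, so the change is wording plus the naming of an instrument. It should be made before enrolment, because a missed baseline cannot be recovered. The downside is that self-report is less objective than a sensor, and in an open trial patients know their arm when they answer. A common measure with that weakness is still more useful for the comparison than a sensor in one arm.

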
## 2. Methods/Design

### 2.1. Primary Objective

The aim of the study is to evaluate the improvement of self-management at home in chronic stroke survivors using the decision support and self-management system for stroke survivors (STARR) (compared with standard of care). Improving the self-management means increasing physical function, controlling risk factors for a new cardiovascular event, improving quality of life, as well as other items, such as self-management behaviors, adherence to treatments indicated by the doctor, improving health care resource utilization, knowledge of the condition, mood, and social isolation. The alternative hypothesis would be that STARR management improves self-management, as well as the quality of life of stroke survivors.

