### 2.3. Participants

Inclusion criteria age 18 years to 80 years;having a diagnosis of first ischemic stroke within the past 6 months;hemiparesis with mild (91-99) or moderate (61-90) disability (Barthel Index, BI);with or without speech pathology but able to understand simple orders (Mississippi Aphasia Screening Test, >45);able to cope and to understand the guidelines to use the devices;the life expectancy of at least 12 months;no severe cognitive impairments (Montreal Cognitive Assessment, MoCA, >26);without medical comorbidities that could interfere with the home-rehabilitation program (for example, severe aortic stenosis, respiratory failure, severe osteoarthrosis);without socio-familiar dystocia (Gijon’s socio-familial evaluation scale (SFES) <14)without a basal functional situation >1 by a Modified Rankin Scale (MRS).

Exclusion criteriamedical comorbidities that could interfere with the home-rehabilitation program.refusal to sign the informed consent and participate in the study.

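### Social isolation is listed as a secondary outcome, but the only instrument assigned to it is a scale the protocol describes as measuring anxiety and depression

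*Protocol article*

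**What the plan says.** Social isolation appears in three places in the protocol article.

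- **Abstract.** It is listed among the outcome measures, next to mood but as a separate item.
- **Section 2.1, Primary Objective.** The explanation of what better self-management means ends with a list of further items, among them "improving health care resource utilization, knowledge of the condition, mood, and social isolation".
- **Section 2.10, Outcome Measures.** Among the secondary outcomes, one bullet reads "Mood and social isolation by Goldberg scale that measures anxiety and depression".

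Table 1, the patient schedule, lists the Goldberg scale as "Depression and Anxiety: Golberg Scale" and marks it at all four visits: event, baseline, first follow-up and final.

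Two other sets of entries in Table 1 bear on the question. The first is "Gijon’s social-familial evaluation scale", which sits in the inclusion block and is marked at the event and baseline visits only. Section 2.3 uses it as an eligibility criterion: "without socio-familiar dystocia (Gijon’s socio-familial evaluation scale (SFES) <14". The second is the quality-of-life entry, "SF-36 Stroke Impact Scale (SIS"), marked at the event, baseline and final visits but not at the 3-month visit.

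**The concern.** The bullet in section 2.10 names two constructs and one tool, then says what the tool measures. That description fits the first construct and leaves the second without a measure. This is not a detail left open for a fuller protocol or an analysis plan to supply: the article does name an instrument for social isolation, and on its own description the instrument measures something else.

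What is at stake is the meaning of one reported result. An analyst who follows section 2.10 would compare Goldberg scores between the groups and could present the difference under the heading of social isolation. A home-based digital intervention might change mood and social contact by different amounts, so a result on one is not evidence on the other. If the mismatch is noticed only at the reporting stage, the remaining route is to pick a substitute from the questionnaires collected. In a trial that section 2.4 describes as open, that would be an outcome defined after the fact.

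**Working it through.** No arithmetic applies. The protocol gives no figure for this outcome, and the point does not depend on a sample size, error rate or effect size. The check is to trace the construct and the candidate instruments through the article.

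**Step 1. Is social isolation declared separately from mood?** Yes. Section 2.1 has "knowledge of the condition, mood, and social isolation" as items in one list, and the abstract lists the same items. Section 2.10 joins mood and social isolation in one bullet but names both.

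**Step 2. What is assigned to it?** Only the Goldberg scale, in section 2.10.

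**Step 3. What does the protocol say that scale measures?** Section 2.10 says anxiety and depression, and Table 1 says depression and anxiety. The two places agree, and neither mentions isolation.

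**Step 4. Is anything else in the schedule designated for it?**

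| Instrument | Stated purpose | Baseline | 3 months | 6 months (final) | Linked to social isolation in the text? |
|---|---|---|---|---|---|
| Goldberg scale | Anxiety and depression | yes | yes | yes | Named for it in 2.10, but described as measuring something else |
| Gijon scale | Eligibility | yes | no | no | No |
| SF-36 | Quality of life | yes | no | yes | No |
| Stroke Impact Scale | Quality of life | yes | no | yes | No |

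No row in Table 1 or in Table 2 (the caregiver schedule) carries social isolation as its label. The Gijon scale is the one explicitly social scale for patients. It gives no value after randomisation, so it cannot serve as an outcome as scheduled.

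**Step 5. What does the item touch?** Section 2.10 places it among the secondary outcomes. The primary outcome there is the Southampton Stroke Self-Management Questionnaire with the family needs questionnaire. The sample size in section 2.13 is built on a proportion of dependence. Neither uses the Goldberg scale or any measure of isolation.

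**Result.** Social isolation is named in three places and has one instrument assigned, which the protocol describes as measuring anxiety and depression. No instrument designated for social isolation is scheduled after baseline.

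**The case against.** The strongest reply is that this is a slip of labelling in one secondary bullet of a small pilot. The sentence itself discloses what the Goldberg scale measures, and Table 1 labels it correctly, so a careful report could simply present the result as anxiety and depression. Section 2.14 gives only general comparison rules and defines no social isolation score or test. Section 2.2 does not list social isolation among the secondary objectives, and section 2.1 mentions it only at the end of a list of examples. Sections 2.3 and 2.6 keep out patients with socio-familial problems or without family support, which suggests that isolation is peripheral in this population.

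Most of this stands as a limit on the weight of the point. It does not remove the mismatch: three places promise a result on social isolation, and the one tool named for it does not measure it.

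The objection also guards against four stronger readings that a reader might draw.

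- **That the trial cannot report on social isolation at all.** The documents do not support this. SF-36 and Stroke Impact Scale data will exist at baseline and at the final visit. What can be said is that the trial cannot report on it with the instrument assigned. Equally, the article never says that either questionnaire covers social isolation, so it cannot be assumed that they fill the gap.
- **That a wrong conclusion is certain.** It is possible. Nothing obliges the authors to report the Goldberg result under that name.
- **That the primary outcome is undermined because section 2.1 is headed as the primary objective.** Section 2.10 assigns the primary outcome to other questionnaires.
- **That failing to repeat the Gijon scale is an error.** It is an eligibility tool, and an eligibility tool need not be repeated after randomisation. It matters only because it shows that no other explicitly social scale is available at follow-up.

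**Conclusion.** The concern holds as an incorrect mapping of instrument to outcome for one secondary item. On the protocol's own description, the scale assigned to social isolation measures anxiety and depression, and nothing else is designated for it after baseline. A Goldberg result could be reported as an effect on social isolation, and that report would not be supported by what was measured.

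The size is modest. One half of one secondary bullet is affected, for all patients at both follow-up visits. The primary outcome, the randomisation, the sample size and the main comparison are untouched. It is still worth correcting, because the correction changes what the trial may claim at almost no cost.

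The conclusion rests on taking the protocol's description of the Goldberg scale at face value. It makes no assumption about the content of the SF-36 or the Stroke Impact Scale.

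**What to change.** 1. In section 2.10, label the Goldberg outcome as anxiety and depression only, as Table 1 already does.
2. Then choose one of two routes for social isolation:
   - **Keep it.** Before any data are seen, pre-specify a measure from an instrument already scheduled at baseline and the final visit. A suitable part of the SF-36 or of the Stroke Impact Scale is one example, if the sponsor confirms that it covers this construct. State the score and the time point.
   - **Drop it.** Remove social isolation from the abstract, from the list in section 2.1 and from the outcome list in section 2.10.

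Either route is a change of wording and adds no visit, patient or questionnaire. Keeping the outcome this way means there is no social measure at the 3-month visit, because Table 1 does not schedule those two questionnaires then. Dropping it means one fewer claimed outcome.
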